### Interventions

Patients in both groups will receive five to eight IA sessions (at least five sessions) for each treatment. After insertion, needles will be left in place for 24 h with a 1-day interval between each session. A full treatment course will constitute four sessions. Acupoint prescription will comprise acupuncture points with three needles for the hands or three needles for the feet combined with nourishing liver and kidney acupoints. Based on the location of joint pain in the limbs, the acupoints of patient with upper limb pain will be treated with three needles combined with tonification of the liver and kidney to consolidate the roots, including Shousanli, Hegu, Zhongzhu, Ganshu, and Shenshu. In patients with lower limb pain, Zusanli, Jiexi, Neiting, Ganshu, and Shenshu will be selected as acupoints for tonification of the liver and kidney (Fig. 3). During the needle retention period, other treatments will not be performed at the acupoints where the needle is retained, and other non-needle locations will not be affected.

**Fig. 3 Fig3:**
[figure not shown]
Locations of acupoints. LI10 (Shou Sanli), 3 cun below the lateral epicondyle of the humerus. ST36 (Zu Sanli), located on the outside of the calf, 3 in. below the calf’s nose. ST41 (Jiexi), in the central depression of the horizontal stripes at the junction of the instep and the calf. ST44 (Neiting), seam between the second and third toes on the dorsum of the foot. BL18 (Ganshu), at the same level as the inferior border of the spinous process of the 9th thoracic vertebra (T9), 1.5 cun lateral to the posterior median line. BL23 (Shenshu), at the same level as the inferior border of the spinous process of the 2nd lumbar vertebra (L2), 1.5 cun lateral to the posterior median line. LI4 (Hegu), on the back of the hand, between the first and second metacarpal bones, the midpoint of the radial side of the second metacarpal bone. SJ03 (Zhongzhu), located on the back of the hand, 2 cm below the base of the little finger and the ring finger, the depression on the back of the hand

### Control intervention

RA patients will receive basic treatment and nursing routines. Basic treatment will comprise oral celecoxib, leflunomide, and methotrexate. Routine nursing measures will encompass lifestyle, diet, medication, psychology, and exercise. Patients will be required to remain vigilant regarding joint warmth and avoid cold stimulation and/or long-term weight-bearing of small joints. Patients will be encouraged to adopt a healthy diet and lifestyle by prioritising nutritious low-salt and low-fat foods, abstaining from fried or spicy food, and quitting smoking and alcohol. Nursing staff will introduce commonly used drugs, basic medication methods, and basic pharmacological effects of clinical drugs to improve patients’ understanding of their daily medication. Patients will be encouraged to stay positive and maintain social interactions. Patients will be encouraged to perform slow or fast walking, square dancing, joint exercises, and other activities, as desired.

The aforementioned intervention acupoints will be treated with pseudo-intradermal needling (placebo). No needles will be present under the adhesive tape of the sham treatment group; the tape will merely be adhered to the surface of acupoints. Patients will be required to press the needle embedding points for 1 to 2 min every 3 to 4 h to simulate an increase in stimulation and efficacy.

### Experimental intervention

Measures for the experimental group will be similar to those for the control group, as described above, with the exception that the experimental group will receive actual needle treatment rather than sham treatment. Acupuncture needles (0.2-mm diameter and 1.2-mm length; Qingling, Japan) will be provided by Sichuan Yuanquan Medical Instrument Co., Ltd., China. The skin will first be disinfected with 75% alcohol. Sealing paper will be removed from an acupuncture needle. Next, the plastic container will be twisted backward. Half of the peeling paper and tape will be clamped with the thumb and forefinger, followed by separation from the other half of the paper and removal of the needle from the plastic container. The needle will be applied directly to the sterilised acupuncture point and inserted. The release paper will be removed, and the tape will be pressed to ensure secure adhesion. Each acupuncture point will be treated according to this procedure. Needles will be removed after 24 h. Patients will be required to press the needle embedding points for 1 to 2 min every 3 to 4 h to promote stimulation and enhance treatment efficacy.

### Outcomes

#### Primary outcomes

Primary outcomes are the evaluation of TCM syndromes before and after a course of treatment and Health Assessment Questionnaire (HAQ) scores.

TCM syndrome evaluation will be conducted according to the 2002 “Guiding Principles for Clinical Research of New Chinese Medicines [17]” based on the degree of joint pain; number of joints involved; joint swelling, tenderness, flexion, and extension; and other symptoms or signs. Scores will be divided into four levels: none, 0 points; light, 1 point; severe, 2 points; and very severe, 3 points. Four types of curative effects will be considered: (1) recovery: TCM syndrome scores decreased by ≥ 70%; (2) significant effect: TCM syndrome scores decreased by ≥ 50%; (3) effective: TCM syndrome scores decreased by ≥ 20%; and (4) ineffective: TCM syndrome scores decreased by less than 20%, whereby effectiveness rate = ([points before treatment – points after treatment]/points before treatment) × 100%.

HAQ scores will be used to assess patients’ physical function [18]. The HAQ is a widely used 20-item questionnaire that encompasses the following dimensions: dressing, washing, standing up, walking, and other aspects of daily life. Each question is scored on a scale from 0 to 3 points (0, no difficulty; 1, some difficulty; 2, very difficult; 3, unable to complete). The total score ranges from 0 to 60 points, and average scores range between 1 and 3 points. Higher scores indicate poorer health status.

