### Power calculation

Sample size was determined based on the formula for sample size calculation comparing two groups with independent sampling rates:
$$ \mathrm{n}1=\mathrm{n}2=\frac{{\left({Z}_{1-\alpha /2}+{Z}_{1-\beta}\right)}^2\left[{P}_1\left(1-{p}_1\right)+{P}_2\left(1-{p}_2\right)\right]}{{\left({p}_1-{p}_2\right)}^2} $$

Based on previous clinical research, the rate for the trial group that received IA for RA treatment was 95% and that of the control group was 78% [16]. In this study, assuming *α* = 0.05 (both sides) and 1 − *β* = 0.80, the required sample size was calculated as 60 per group. Considering a dropout rate of 10%, we concluded that the required sample size was 66 per group. Therefore, a total of 132 patients with RA will be recruited.

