### Data analysis

Data analysis will be performed using SPSS software (version 23.0; IBM SPSS Statistics, New York, USA) by statisticians independent of the research team.

Baseline data including age, sex, disease duration, evaluation of TCM syndromes, HAQ score, DAS28 score, and CRP values before interventions will be compared between the two groups. All analyses will be strictly conducted according to the intention-to-treat principle. Continuous variables such as age, disease course, and values of DAS28, HAQ, and CRP will be presented as mean ± standard deviation (SD). Categorical variables such as TCM syndromes will be presented as percentages. Student’s *t* tests will be used to compare quantitative data between the two groups. Data on adverse reactions will be analysed using the *X*^2^ test. Differences will be considered statistically significant at *P* < 0.05. Missing data will be imputed by multiple imputation. To assess the robustness of the results, a sensitivity analysis using a pattern-mixture model will be used.

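### Two primary outcomes share one unadjusted 0.05 threshold and a sample size built on a single rate comparison, so the stated 5% error and 80% power cannot both describe trial success until a success rule is fixed

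*Protocol article*

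**What the plan says.** The abstract and the Primary outcomes section of the protocol article both name two primary outcomes: "Primary outcomes are the evaluation of TCM syndromes before and after a course of treatment and Health Assessment Questionnaire (HAQ) scores". The Data analysis section treats them as different kinds of variable. TCM syndromes are categorical and reported as percentages. HAQ is continuous and reported as mean and standard deviation.

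That section gives one rule for significance: "Differences will be considered statistically significant at *P* < 0.05". It gives no split of alpha, no order of testing and no statement that both outcomes must succeed.

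The Power calculation section uses a single comparison of proportions: "Sample size was determined based on the formula for sample size calculation comparing two groups with independent sampling rates". Its inputs are two rates: "the rate for the trial group that received IA for RA treatment was 95% and that of the control group was 78" (per cent). With two-sided alpha 0.05 and power 0.80, "the required sample size was calculated as 60 per group", raised to 66 for dropout and 132 in total. The section does not name the outcome these rates belong to. HAQ does not enter the calculation.

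**The concern.** A trial with two primary outcomes needs a rule that turns two results into one conclusion. Two rules are common, and they have opposite costs. If either outcome is enough, there are two chances of a false positive at 0.05, so the overall error exceeds 5%. If both are needed, the error stays within 5%, but the trial must win twice and its chance of success falls below the power of the harder test.

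The article's figures are those of a trial with one primary outcome: all of alpha and all of the power go to one comparison. Under neither rule do the stated 5% and 80% both describe trial success. What is at stake is how a mixed result is read. On the published text, significance on one primary outcome and not on the other has no agreed meaning.

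**Working it through.** **Inputs.** From Power calculation: p1 = 0.95, p2 = 0.78, two-sided alpha 0.05, power 0.80, 60 per group before dropout. From Primary outcomes: two primary outcomes. From Data analysis: threshold 0.05. Assumed, because the article gives none: the correlation between the two test statistics, the HAQ effect in SD units, and the HAQ power.

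**1. The plan's own figure.** The article's formula is n = (z for 1 − alpha/2 + z for power)² × [p1(1 − p1) + p2(1 − p2)] / (p1 − p2)².
- Variance term: 0.95 × 0.05 + 0.78 × 0.22 = 0.0475 + 0.1716 = 0.2191.
- n = (1.960 + 0.842)² × 0.2191 / 0.17² = 59.50, rounded up to 60. The stated figure reproduces.
- Power at 60 per group: the standard error is √(0.2191/60) = 0.0604, and 0.17/0.0604 − 1.960 = 0.853, which gives 80.3%.

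**2. Either outcome suffices, each at 0.05.** With independent tests the family-wise error is 1 − 0.95² = 0.0975. For correlated two-sided tests, a bivariate normal model gives:

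| Assumed correlation | Family-wise error |
|---|---|
| 0 | 9.75% |
| 0.3 | 9.5% |
| 0.5 | 9.1% |
| 0.7 | 8.3% |
| 0.9 | 7.0% |

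Every value is above 5%. In this model the independent case is the largest.

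**3. Either suffices, with alpha split to 0.025 each.**
- Power of the rate comparison at 60 per group: 0.17/0.0604 − 2.241 = 0.572, which gives 71.6%.
- Restoring 80%: n = (2.241 + 0.842)² × 0.2191 / 0.17² = 72.06, so 73 per group.
- With the article's own 10% addition: 73 × 1.1 = 80.3, so 81 per group or 162 in total, against 132 planned.

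**4. Both required, each at 0.05.** The error is at most 5%. Joint power cannot exceed the power of the weaker test. If each test had 80% power:

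| Assumed correlation | Power to win both |
|---|---|
| 0 | 0.80² = 64% |
| 0.5 | 69% |
| 0.7 | 71% |
| 0.9 | 75% |

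**5. How far 80% for HAQ can be supported.** With 60 per group, the difference detectable with 80% power at 0.05 is (1.960 + 0.842) × √(2/60) = 0.51 SD. Assumed HAQ effects of 0.3, 0.4 and 0.5 SD give 38%, 59% and 78% power. The article supplies nothing with which to choose among these.

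**6. Fixed sequence, rate outcome first.** If the first null hypothesis is true, any false claim requires rejecting it, which has probability of at most 5%. If the first null is false, the only possible false claim is on HAQ, again at most 5%. The first test keeps the full 0.05, so 60 per group and 80.3% power stand for it.

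**The case against.** The strongest reply is that this is a condensed article. The full protocol or an analysis plan may hold a success rule, and an article's silence on multiplicity is not an error. That stands as far as it goes. A reader might infer that the investigators are free to choose the reading after seeing the data; the article does not show this, because a document not at hand may fix the rule. What remains is on the page: two primary outcomes, one general threshold, and a sample size that gives all of alpha to one of them. A rule kept elsewhere could settle the reading, but an alpha split would leave about 72% power at 60 per group, and a both-required rule would rest on an HAQ power for which the article gives no inputs.

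A reader might also infer that the trial's false-positive rate is near 10%. That holds only if either outcome counts as success and the correlation is low. The TCM score covers joint pain, tenderness and movement, and HAQ covers daily function, so positive correlation is plausible and lowers the figure. If both are required, the error does not exceed 5%.

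Two further cautions stand. The Power calculation section never says that its rates are TCM rates; this is inferred from HAQ being continuous. And the Data analysis section names a chi-square test only for adverse reactions, so no test is tied to the TCM categories. Applying 0.05 to them relies on the general rule.

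Finally, fixed sequence, co-primary testing, an alpha split and demoting one outcome are all legitimate. The documents do not dictate one.

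**Conclusion.** The concern holds in conditional form. If either outcome suffices, the family-wise error is above 5%: 9.75% under independence and about 9.5% to 7.0% at assumed correlations of 0.3 to 0.9. If both are needed, the error is controlled, but the stated 80% is not the probability of trial success. The 64% to 75% range rests on an 80% HAQ power granted for illustration, so it is not a measured shortfall. The true figure could be lower or, with a large HAQ effect, closer to the power of the rate comparison.

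It would be too strong to say that the sample size is miscalculated. Sixty per group is right for the rates, alpha and power stated. It would also be too strong to say that the 80% demonstrably belongs to the TCM outcome; that is probable but not stated. This should be fixed, but it does not undermine the design, because at least one acceptable rule keeps the planned numbers.

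**What to change.** Before unblinding, state in the analysis section which result on the two primary outcomes counts as success.

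The option that keeps 60 per group is a fixed sequence:
- First, test the rate outcome on which the trial was sized, at two-sided 0.05. The sponsor should confirm what this outcome is. Presumably it is the proportion of patients whose TCM score falls by at least 20%. It should then be defined as a responder rate, because the Primary outcomes section lists four effect categories and defines its effectiveness rate as a patient's percentage change, not as a proportion of patients. The test should be named with it.
- Then test HAQ at two-sided 0.05 only if the first test is significant. Otherwise report HAQ descriptively.
- State that the 80% power refers to the rate outcome alone.

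If the sponsor prefers another rule, its sizing should be shown: about 73 per group before dropout for an equal alpha split on the rate outcome, or an HAQ difference and SD with the resulting joint power if both must succeed.

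The fixed sequence costs one paragraph and no patients. Its downside is that HAQ cannot be claimed confirmatorily if the first test fails.

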#### Secondary outcomes

Secondary outcomes are DAS28 and CRP levels. For DAS28, general health (GH), 28-joint swelling index (SJC), joint tenderness count (TJC), erythrocyte sedimentation rate (ESR), and visual analogue scale (VAS) scores will be evaluated. The 28 joints include the shoulder, elbow, wrist, metacarpophalangeal, proximal interphalangeal, and knee joints. The formula is as follows [19]:
$$ \mathrm{DAS}28-\mathrm{ESR}=0.56\times \sqrt{\left(\mathrm{TJC}28\right)}+0.28\times \sqrt{\left(\mathrm{SJC}28\right)}+0.70\times \ln \left(\mathrm{ESR}\right)+0.014\times \mathrm{GH}. $$

The level of disease activity will be categorised as follows: remission (≤2.6), low activity (>2.6 and ≤3.2), moderate activity (>3.2 and ≤5.1), and high activity (>5.1).

CRP is a non-specific marker of systemic inflammation that directly reflects the degree of inflammation and infection. CRP is widely used in clinical diagnosis and assessment of treatment efficacy for rheumatic and autoimmune diseases, especially during the active stage of the disease. Higher serum CRP levels indicate greater disease severity.

### Patient safety

To guarantee patient safety, acupuncture treatment will be performed in the rheumatology department to ensure that rheumatologists and first-line physicians will be able to respond to emergencies in a timely manner. Adverse events such as pain, dizziness, pruritus, and local redness will be carefully recorded in case report forms (CRFs). Serious adverse events such as death or life-threatening events will be immediately reported to the principal investigator.

### Practitioner training and quality control

Practitioners and press needle operators will be required to undergo rigorous training and consistency testing to ensure consistency in comprehension and implementation of interventions. All acupuncture manipulations will be performed by two licensed head nurses with at least 5 years of TCM clinical experience. Two team members will inspect measurements during progress. Data analysts will not participate in clinical implementation and project design to ensure appropriate blinding.

### Data management

Data will be recorded using printed CRFs. Relevant electronic records will be assessed and entered by two team members. Only outcome assessors will have access to CRFs and will perform data entry. When patients suffer death or life-threatening serious adverse events, our researchers will immediately report to main investigators, although serious adverse events will not be anticipated. The main investigators will make the final decision to terminate the trial after comprehensive discussion.

The data monitoring committee of the Rheumatology Department in the First Affiliated Hospital of Guangzhou University of Chinese Medicine which is independent from the funder and any competing interests will set up to monitor regularly the performance and safety of the trial. It is composed of independent clinical experts and statisticians. They will check the randomly assigned participants meet the inclusion and exclusion criteria, ensure the trial is proceeding smoothly, and inspect adequate data is recorded in the CRFs. There will be no interim analysis. This trial will continue until the 132 participants have completed this trial.

### Adherence improvement

Before the participants are enrolled in the study, our researchers will inform the patient of the study information, including study objectives, intervention measures, treatment time, benefits, and potential risks. These lay the foundation for patient compliance. During the intervention period, our researchers will instruct patients to press the needle embedding points for 1 to 2 min every 3 to 4 h to simulate an increase in stimulation and efficacy. Two team members will also inspect measurements during progress for monitoring adherence. The data monitoring committee will also inspect data is adequately recorded in the CRFs. If patients suffer an adverse event, our rheumatologists and first-line physicians will respond to emergencies in a timely manner and provide free medical guidance. After all follow-ups, we will provide 3 months of free intradermal acupuncture for patients in the sham group. All treatment and examination costs in this study are free and borne by the team. Certain transportation subsidies will also be provided. These will contribute to improving adherence.

### Confidentiality

All researchers will sign a confidentiality agreement to protect the privacy of participants. Patient’s medical records and CRFs are kept in the hospital as required and they will be retrieved when necessary. Patient’s information and illness will not be discussed in public. Patient’s personal information will not be provided to other institutions or individuals. Besides, data will be anonymised prior to publication to prevent identification of individual participants.

### Data analysis

Data analysis will be performed using SPSS software (version 23.0; IBM SPSS Statistics, New York, USA) by statisticians independent of the research team.

Baseline data including age, sex, disease duration, evaluation of TCM syndromes, HAQ score, DAS28 score, and CRP values before interventions will be compared between the two groups. All analyses will be strictly conducted according to the intention-to-treat principle. Continuous variables such as age, disease course, and values of DAS28, HAQ, and CRP will be presented as mean ± standard deviation (SD). Categorical variables such as TCM syndromes will be presented as percentages. Student’s *t* tests will be used to compare quantitative data between the two groups. Data on adverse reactions will be analysed using the *X*^2^ test. Differences will be considered statistically significant at *P* < 0.05. Missing data will be imputed by multiple imputation. To assess the robustness of the results, a sensitivity analysis using a pattern-mixture model will be used.

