## Methods/design

### Aim

The aim of this study will be to design a detailed research protocol for IA treatment for RA patients in China and to explore its clinical efficacy, adverse reactions, and safety.

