### Randomisation

RA patients who meet the inclusion criteria and agree to participate in this research will be randomly allocated to either the intervention group or control group, with an allocation ratio of 1:1. The random allocation sequence will be generated by a statistician (not involved in the study) using a computer programme. Each random number with a group assignment will be written on a piece of paper and inserted into a sealed envelope. Following baseline assessment, participants will be provided with an envelope according to the randomisation sequence.

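### Strict intention-to-treat is fixed for every analysis, adverse reactions included, so the harm rate of intradermal acupuncture can be diluted by patients who never had a needle applied

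*Protocol article*

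**What the plan says.** Three statements in the Data analysis section of the protocol article bear on this.

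- The population rule: "All analyses will be strictly conducted according to the intention-to-treat principle".
- The safety test: "Data on adverse reactions will be analysed using the" chi-square test. No separate population, denominator or grouping is named for it.
- The missing-data rule: "Missing data will be imputed by multiple imputation". The variables are not listed. The next sentence adds a pattern-mixture sensitivity analysis.

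Elsewhere, the Aim section makes safety an objective: the trial is "to explore its clinical efficacy, adverse reactions, and safety". The Randomisation section places allocation before treatment: "Following baseline assessment, participants will be provided with an envelope according to the randomisation sequence". The Control intervention section describes the sham as adhesive tape with no needle beneath it. The Patient safety section has adverse events such as pain, dizziness, itching and redness entered on case report forms.

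**The concern.** Keeping all randomised patients in their assigned arm protects an efficacy comparison. For harm the same rule works differently. A reaction to a needle can arise only in someone who had one. An IA patient who leaves between opening the envelope and the first session adds to the denominator but cannot add a needle reaction to the numerator. If a sham patient were needled by mistake, any resulting reaction would count against sham. Both bring the arms closer together, which is cautious for efficacy but not for safety.

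Silence about a safety population would be no finding, since an analysis plan commonly defines it. Here the text is not silent: the rule is stated for all analyses, and strictly. An analysis plan that later defined a treated-patients safety set would contradict the published article. At stake is the adverse-reaction rate reported for IA, in a trial that sets out to establish its safety.

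**Working it through.** **Inputs from the document (Power calculation).** Response rates of 95% and 78%; "assuming *α* = 0.05 (both sides) and 1 − *β* = 0.80"; 10% dropout; 66 per group, 132 in total.

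**Inputs that are assumptions.** The document gives no adverse-reaction rate and does not split the dropout into before and after the first needle. I take rates of 10%, 20% and 30% among needled patients, and k = 0, 1, 3 or 7 IA patients never needled.

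**Step 1: reproduce the plan's own figure.** With the plan's formula, n = (1.960 + 0.842)² × [0.95 × 0.05 + 0.78 × 0.22] / (0.95 − 0.78)² = 7.849 × 0.2191 / 0.0289 = 59.5, rounded up to 60 per group. Then 60 × 1.10 = 66 per group and 132 in total, as stated. The planned dropout is 66 × 0.10 = 6.6, so about 7 per group. This sets the upper end of k.

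**Step 2: dilution of the IA rate.** If never-needled patients are counted as event-free, the reported rate is the rate among needled patients × (66 − k)/66. The relative loss is k/66.

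| k | Relative loss | 10% reads | 20% reads | 30% reads |
|---|---|---|---|---|
| 0 | 0% | 10.0% | 20.0% | 30.0% |
| 1 | 1.5% | 9.8% | 19.7% | 29.5% |
| 3 | 4.5% | 9.5% | 19.1% | 28.6% |
| 7 | 10.6% | 8.9% | 17.9% | 26.8% |

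**Step 3: effect on the comparison.** Take illustrative counts of 12 IA and 4 sham patients with a reaction. Under strict intention-to-treat the comparison is always 12/66 v 4/66: risk ratio 3.0, uncorrected chi-square p = 0.033. The treated-patients comparison depends on where the untreated patients are:

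- 7 untreated in each arm: 12/59 v 4/59, ratio 3.0, p = 0.031.
- 7 untreated in the IA arm only: 12/59 v 4/66, ratio 3.4, p = 0.017.
- 7 untreated in the sham arm only: 12/66 v 4/59, ratio 2.7, p = 0.057.

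No event leaves the numerator in any of these. Even with all 7 untreated patients in one arm, the ratio moves only between 2.7 and 3.4. These counts were chosen near the 0.05 boundary, so small shifts in p show clearly.

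**Step 4: multiple imputation.** Suppose event status were imputed for 7 IA patients. Imputing within arm, under missing at random, leaves the expected rate unchanged: (0.20 × 59 + 0.20 × 7)/66 = 20%. If the imputation model ignored arm, and the sham rate were an assumed 2%, the imputed patients would carry (20% + 2%)/2 = 11%. The IA rate would then be (0.20 × 59 + 0.11 × 7)/66 = 19.0%. The document does not say that the model ignores arm.

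**The case against.** The strongest reply is that the problem may never occur. Patients are inpatients, allocated after baseline assessment and treated in the rheumatology department. The groups are treated in separate rooms by two trained operators. Few may go unneedled, crossover may be nil, and a safety set is commonly left to the analysis plan. This stands as an argument about size and severity. It does not remove the point, because the sentence as written already settles the population for every analysis.

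Four stronger readings are tempting, and the document does not support them.

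- A reader might infer that the IA harm rate will in fact be diluted. That needs patients who are never needled, and no number is given; at k = 0 there is no dilution.
- A reader might infer that multiple imputation by itself pulls the IA rate towards sham. Nothing says that event status is imputed; the sentence is general and merely does not exclude it. Within-arm imputation leaves the expected rate unchanged, and the planned pattern-mixture analysis is aimed at departures from missing at random. Nor do the two mechanisms add up for the same patient: one who was never needled is either counted as event-free or has a status imputed.
- A reader might infer that the shift always favours IA. It can be zero, and untreated patients in the sham arm alone move the comparison the other way (step 3).
- A reader might infer that an attribution step biases the comparison, because events are recorded but reactions are tested. The article describes no such step. The terms are used loosely, and causality rules commonly sit in the full protocol.

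**Conclusion.** The point holds as a low-severity one. As worded, the article commits the adverse-reaction comparison to all randomised patients by assigned arm, which is a poor choice for harm when safety is a stated aim. The possible understatement of the IA rate runs from nothing to about 10.6% relative. The upper end assumes that all of the planned dropout in the IA arm, about 7 of 66, happens before the first needle and that those patients are counted as event-free. The event rates used are also assumptions. The effect on the between-group test is small. The efficacy analyses and the sample size are unaffected.

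**What to change.** In the Data analysis section, limit strict intention-to-treat and multiple imputation to the efficacy outcomes. State that adverse reactions are analysed on observed events, without imputation, in patients who had at least one needle or tape application, grouped by what was applied, and that the number with unknown event status is shown for each group.

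This takes about two sentences and needs no new data or patients. The downside is that the safety and efficacy denominators may differ by a few patients, which a participant flow table can explain. The change should be made and dated before the allocation is unblinded.

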**Methods:**

This study is a randomised, sham-controlled, patient-outcome assessor-statistician blind trial that aims to evaluate the effects of IA in patients with RA. We will recruit 132 patients aged ≥ 18 years with a diagnosis of RA. Patients will be randomly allocated with a 1:1 ratio to IA or sham IA groups. Both groups will receive basic treatment and nursing routines for RA. The experimental group will receive actual IA treatment, whereas the control group will receive sham IA treatment. All patients will receive one course of treatment (i.e., four consecutive treatment sessions with an intervening 1-day interval). Primary outcomes will be traditional Chinese medicine (TCM) syndromes before and after a treatment course and Health Assessment Questionnaire (HAQ) scores. Secondary outcomes will be disease activity score 28 (DAS28) and levels of serum C-reactive protein (CRP). Outcome measures will be collected pre- and post-treatment.

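### HAQ, DAS28 and CRP are to be compared by t tests with no baseline adjustment, which gives up precision that the already collected baseline values could supply

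*Protocol article*

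**What the plan says.** The Data analysis section of the protocol article names one between-group method for quantitative data: Student's t "tests will be used to compare quantitative data between the two groups". The same paragraph identifies the variables: "Continuous variables such as age, disease course, and values of DAS28, HAQ, and CRP will be presented as mean" with SD. HAQ is one of two primary outcomes: "Primary outcomes are the evaluation of TCM syndromes before and after a course of treatment and Health Assessment Questionnaire (HAQ) scores". The other two continuous outcomes are secondary: "Secondary outcomes are DAS28 and CRP levels".

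Baseline values are available for all three. The abstract states: "Outcome measures will be collected pre- and post-treatment". The Randomisation section places baseline before allocation: "Following baseline assessment, participants will be provided with an envelope according to the randomisation sequence". The Participants section also lists CRP and DAS28 among the examinations before inclusion.

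The only use given to these values is a comparison of the groups at entry: "HAQ score, DAS28 score, and CRP values before interventions will be compared between the two groups". No ANCOVA, regression or other adjustment of the treatment effect appears anywhere. Multiple imputation and a pattern-mixture sensitivity analysis are planned, but neither is described as adjusting for baseline. The text does not say whether the t tests are on post-treatment values or on change.

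**The concern.** Patients who enter with worse function or more inflammation tend to leave with worse values too. A t test on post-treatment values leaves that between-patient variation in the standard error. A t test on change removes some of it, but over-corrects whenever the pre-post correlation is below 1. Either way, part of any chance baseline difference passes into the estimated effect. The Randomisation section describes no stratification by baseline severity, and the planned baseline comparison comes with no stated action if a difference appears.

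The point matters most for HAQ. It is a primary outcome, but the Power calculation section sizes the trial on response rates only, so the precision of the HAQ comparison has not been planned. The unspecified form of the t test adds to this, because two analyses with different precision both fit the text.

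**Working it through.** **1. The plan's own figure.** Inputs from the Power calculation section: 95% v 78%, two-sided alpha 0.05, power 0.80.

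n = (1.960 + 0.842)² × [0.95 × 0.05 + 0.78 × 0.22] / (0.95 − 0.78)² = 7.849 × 0.2191 / 0.0289 = 59.5, rounded up to 60 per group.

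The stated 60 reproduces, and 60 × 1.10 = 66 as stated. This figure concerns a response rate and does not size HAQ, DAS28 or CRP.

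**2. Assumptions.** The documents give no SD, target difference or pre-post correlation r for the three outcomes. I take r = 0.3, 0.5 and 0.7, equal SDs before and after, and 60 evaluable patients per group.

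**3. Formulas.** Variance of the treatment effect relative to a post-value t test:

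- post-value t test: 1
- change-score t test: 2(1 − r)
- ANCOVA: 1 − r²
- ANCOVA against change score: (1 − r²) / [2(1 − r)] = (1 + r)/2

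The reference is the standardised difference at which a post-value t test has 80% power: 2.802 × √(2/60) = 0.511 SD. Power for a method with relative variance V is Φ(2.802/√V − 1.960).

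**4. Results.**

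| | r = 0.3 | r = 0.5 | r = 0.7 |
|---|---|---|---|
| Variance, ANCOVA v post-value | 0.91 | 0.75 | 0.51 |
| Variance, change v post-value | 1.40 | 1.00 | 0.60 |
| Variance, ANCOVA v change | 0.65 | 0.75 | 0.85 |
| Power, post-value t test | 80% | 80% | 80% |
| Power, change-score t test | 65.8% | 80.0% | 95.1% |
| Power, ANCOVA | 83.6% | 89.9% | 97.5% |
| ANCOVA patients per group matching 60 with a post-value t test | 55 | 45 | 31 |

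Worked line for r = 0.5: 2.802/√0.75 − 1.960 = 1.275, and Φ(1.275) = 0.899.

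**5. Chance imbalance.** The baseline difference between groups has a standard error of √(2/60) = 0.183 SD. An imbalance of that size shifts a post-value comparison by r × 0.183 = 0.05, 0.09 or 0.13 SD. It shifts a change-score comparison the other way by (1 − r) × 0.183 = 0.13, 0.09 or 0.05 SD. ANCOVA removes this shift when the relation to baseline is linear.

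**6. Cost of the covariate.** One degree of freedom raises the variance by a factor of about 1 + 1/(120 − 4) = 1.009. This is recovered once r² exceeds about 0.009, that is, r of about 0.1.

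**The case against.** The strongest reply is that nothing here is an error. Under 1:1 randomisation the t test gives an unbiased estimate and controls type I error, and covariates are often left to a statistical analysis plan. The first part stands: a reader might infer that the planned tests are biased or invalid, and they are not. The second does not remove the point, because the article names the t test as the between-group method, so a plan that adjusted for baseline would depart from it.

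Second, the size of the gain is unknown. A reader might infer that 80% power would simply become 90% or more. That needs a post-value comparator and r of at least 0.5, and the documents supply neither. The before-and-after wording of the TCM outcome makes a change-score test plausible. Against that, the gain at r = 0.7 is only 95.1% to 97.5%, and against a post-value test at r = 0.3 it is only 80% to 83.6%. Nor is the 80% a stated power for these outcomes. It is a reference point, so it cannot be concluded that HAQ is underpowered or that 132 patients is wrong.

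Third, a high correlation might be inferred from a short course in stable disease. Stability is not stated: these are inpatients on active drug treatment. The Interventions section gives both five to eight sessions and a four-session course, which must be reconciled before the interval is known. Entry is limited to mild or inactive disease by DAS28, which narrows its baseline spread and may lower r. CRP may be too skewed for a linear model on the raw scale.

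These points limit the size of the gain. They do not reverse its direction: under the stated assumptions, ANCOVA is at least as efficient as either t test, apart from one degree of freedom.

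**Conclusion.** The point holds as a recommended improvement in efficiency, for a method that the article itself fixes. The planned t tests are valid. What they give up is precision and protection against chance baseline imbalance, most importantly for HAQ.

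The direction is secure and the magnitude is not. For an assumed r from 0.3 to 0.7 with equal SDs, the variance reduction is 9% to 49% against a post-value t test, and 35% down to 15% against a change-score t test. For DAS28 the gain may be at the lower end or below. The stated sample size is not affected, since it rests on response rates.

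**What to change.** Before unblinding, amend the Data analysis section so that HAQ, DAS28 and CRP are each analysed by a linear model of the post-treatment value on treatment group and the same outcome's baseline value. Report the adjusted difference with its 95% CI. If CRP is skewed, model it on the log scale before and after treatment and report the effect as a ratio. Use the same model within the planned multiple imputation. This also settles whether the comparison is of post-treatment values or of change.

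No parallel logistic model for TCM response is needed. That definition already divides by the baseline score, and at the assumed rates only about 60 × 0.05 = 3 and 60 × 0.22 = 13 non-responders per group are expected.

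The cost is a sentence or two of text. No extra patients, visits or measurements are required, and the SPSS version already named can fit the model. The statistical cost is one degree of freedom, about 0.9% of the variance.
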